### Measurement instruments

Several measurement instruments are included in the t0, t1 and t2 questionnaire, as presented in Table 2. Alcohol consumption will be measured using substance use subscales of the 'European Addiction Severity Index' (EuropASI) [15] and Timeline-Follow-Back for alcohol consumption [16]. This Timeline-Follow-Back method has good capacity to retrieve drinking history in the past week [17]. As a third scale to measure alcohol consumption burden the AUDIT is included [18].

**Table 2 T2:** Measurement instruments

**Instrument**	**t0 measure**	**t1 measure**	**t2 measure**
EuropASI (subscales)	x	x	x
Timeline-follow-back	x	x	x
AUDIT	x	x	x
QOL	x	x	x
EQ-5D	x	x	x
WAI-work	x	x	x
SF-HLQ	x	x	x
BSI	x	x	x
MCSDS	x		
Dutch mental health thermometer		x*	x*
WAI		x*	x*

Quality of life will be measured using two instruments: The EQ-5D [19-21] and the QOL [22]. The EQ-5D is a highly accepted, widely used and easy to administer instrument for measuring quality of life for alcohol and drug dependents [23,24]. As the scoring algorithm of the EQ-5D generates an index weighted by a preference measure, EQ-5D scores can be used in cost-effectiveness analysis to estimate QALYs [25]. However, it is recommended that the EQ-5D is used in combination with other quality of life instruments. This should be done to minimize its potential limitation in sensitivity until further results confirm EQ-5D validity in alcohol dependent individuals [26]. Therefore, the 'Quality Of Life' scale QOL [22] is included. According to content validity analysis, this is a valid instrument for measuring quality of life across patient groups and cultures. It is conceptually distinct from health status or other causal indicators of quality of life [27].

### Primary and secondary outcome measures

Primary outcome measures are the differences in alcohol consumption, and the number of participants showing 'treatment response', as defined below. Although de facto a composite score of primary and secondary outcomes, 'treatment response' is considered primary outcome as well. Secondary outcome measurements are AUDIT-score; quality of life as measured by QOL, and EQ-5D, psychopathological symptoms as measured by BSI and ability to work as measured by SF-HLQ and WAI-work.

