**Methods:**

This paper presents the protocol of a three-arm randomized clinical trial to test the (cost-) effectiveness of online treatment for problem drinkers. Self-help online, therapy online and a waiting list are tested against each other. Primary outcome is change in alcohol consumption. Secondary outcome measures include quality of life and working ability. Incremental cost-effectiveness ratios for self-help online alcohol and therapy online alcohol will be calculated. The predictive validity of participant characteristics on treatment adherence and outcome will be explored.

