## Methods

### Aims of the trial

This study aims to test the effectiveness and cost-effectiveness of SOA and TOA against a waiting list control group, in a three-arm randomized clinical trial. Primary outcome measure is the change in alcohol consumption from baseline (t0) to the three month follow-up (t1) and to the six month follow-up (t2). Secondary outcome measures are changes in AUDIT scores, quality of life and quality of functioning at work. Incremental cost-effectiveness ratios for SOA and TOA will be calculated. The predictive validity of participant characteristics on treatment adherence and outcome will be explored.

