### Power calculation

Appropriate sample size is estimated using Gpower v.3.0.5 software [34]. This calculation is based on the primary outcome measure (alcohol consumption), in a one-way ANOVA test design. Based on [10] we expect an effect-size of *d *= 0.40 when comparing waiting list control and treatment groups. To be able to detect even smaller differential effects (*d *= 0.25) between SOA en TOA with *α *= .05 and *β *= .20, we aim to include 150 participants. The power calculation is summarized in Table 3.

**Table 3 T3:** Power analysis

F tests – ANOVA: Fixed effects, omnibus, one-way		
Analysis:	A priori: Compute required sample size	
Input:	Effect size f	0.25
	α error probability	0.05
	Power (1-β error probability)	0.80
	Number of groups	3
Output:	Non-centrality parameter λ	9.938
	Critical F	3.054
	Numerator df	2
	Denominator df	156
	Total sample size	159
	Actual power	0.805

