### Data analysis

Multiple imputation missing data handling procedures will be implemented using MICE [45] a package for the R Statistical Software Environment. As the quantity of consumed alcoholic drinks is the primary outcome variable in this trial, analysis techniques are chosen that suit the expected data distribution. Baseline measurements of the three trial arms will be compared using t-tests and χ^2^-tests. Trial arm differences on primary and secondary outcome variables at three months are tested using repeated measures ANOVA. Trial arm differences for SOA and TOA between t1 and t2 are tested with a 2 (group) × 2 (time) repeated measures ANCOVA with between and within contrasts. Effect-sizes will be calculated using Cohen's *d *[46]. Trial arm differences on treatment-response will be tested using multiple logistic regression analysis. Costs from TOA and SOA will be derived from cost records of the collaborating SATC. Costs will be assessed in correspondence to the recommendations by the U.S. Panel on Cost-effectiveness in Health and Medicine [25], following a macro-costing approach. QALYs will be calculated from the EQ-5D questionnaire, using algorithm by Dolan [47], retrieved from the Open Health Measures website [48]. Based on these estimations, costs-per-QALY and an incremental cost-effectiveness ratio can be calculated. The U.S. Panel on Cost-effectiveness has recommended that cost-effectiveness studies should conduct sensitivity analysis, which for this cost-effectiveness analysis will be implemented through the bootstrap method [49-51].

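### Treatment response is made a second primary outcome in one section, while four other sections name alcohol consumption as the only one and no stated rule links the two

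*Protocol article*

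**What the plan says.** Four places in the protocol article name one primary outcome:

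- Abstract, Methods: "Primary outcome is change in alcohol consumption".
- Aims of the trial, also in the singular: "Primary outcome measure is the change in alcohol consumption from baseline (t0) to the three month follow-up (t1"; the sentence goes on to add the six-month follow-up.
- Power calculation: "This calculation is based on the primary outcome measure (alcohol consumption), in a one-way ANOVA test design".
- Data analysis: "As the quantity of consumed alcoholic drinks is the primary outcome variable in this trial".

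The section on primary and secondary outcome measures names two: "Primary outcome measures are the differences in alcohol consumption, and the number of participants showing 'treatment response', as defined below". It then confirms that this is deliberate: "Although de facto a composite score of primary and secondary outcomes, 'treatment response' is considered primary outcome as well".

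The two outcomes are analysed separately. Data analysis assigns repeated measures ANOVA to consumption at three months and logistic regression to treatment response. Research questions Q1a and Q1d (consumption) and Q1c and Q1f (response) ask for the same three arm comparisons: TOA with SOA, TOA with waiting list, and SOA with waiting list. The only significance level in the article is the .05 in the power calculation, which concerns consumption.

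**The concern.** Which outcome decides the trial should be settled once, before results are seen. Here it is settled in two ways.

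The two outcomes can disagree. Response requires consumption below a sex-specific weekly limit (21 units for men, 14 for women) and less than 10% worsening on every secondary measure. Mean consumption can fall without more people crossing the limit. Response can also differ between arms through the secondary measures when consumption does not. After a split result, one reader could cite the Aims and another the outcomes section, and each would be quoting the protocol correctly.

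Two primaries, each able to support a positive conclusion, also raise the chance of a false one above the nominal level. Response has no sample-size basis of its own.

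**Working it through.** **1. The plan's own figure.** Inputs from Table 3: three groups, f = 0.25, α = .05, power .80. With λ = N·f² and degrees of freedom 2 and N − 3, N = 159 gives λ = 159 × 0.0625 = 9.94, critical F = 3.054 and power 0.805. Table 3 is reproduced, and it covers consumption only.

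**2. Two primaries, each with one three-arm test at .05.** If the outcomes were independent, the chance of at least one false positive is 1 − (1 − .05)² = 1 − .9025 = 9.75%. Correlation lowers it.

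**3. Simulation under no arm differences** (1,000,000 draws). Each outcome has three independent standard normal arm means m₁, m₂, m₃. The two outcomes are correlated ρ within arm. The three-arm test rejects if Σ(mᵢ − m̄)² exceeds the 95% point of χ² with 2 df. A pairwise contrast rejects if |mᵢ − mⱼ|/√2 > 1.96. The documents give no ρ, so the range is shown.

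| Rule | ρ = 0 | ρ = 0.5 | ρ = 0.7 | ρ = 0.9 |
|---|---|---|---|---|
| Either three-arm test significant | 9.7% | 9.1% | 8.5% | 7.1% |
| Any of six ungated two-sided contrasts | 23.0% | 21.3% | 19.6% | 16.7% |
| The same six, hypothesised direction only | 12.8% | 11.6% | 10.7% | 9.1% |

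On one outcome alone, three ungated two-sided contrasts give about 12%.

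A second simulation used 50 per arm and a yes/no response, with an assumed 30% response rate and ρ on the scale underlying response. It gave 8.5 to 9.7% for the first row and 19.4 to 22.7% for the second, over ρ from 0.9 to 0. The picture is the same. Dichotomising weakens the correlation, so the lower ends sit higher.

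**4. One primary, three-arm test first.** If all three arms are equal, nothing is claimed unless the three-arm test rejects, which happens 5% of the time. If exactly two arms are equal, only one true null contrast remains, and it is tested at .05. Either way the familywise error is at most 5%, with α and the Table 3 N as they stand.

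**5. Keeping both, with .025 each.** The same ANOVA at α = .025 has power 0.686 at the planned N = 150 and 0.717 at N = 159. It needs N = 189 for power of at least .80.

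**The case against.** The strongest reply is that multiplicity rules are commonly left to an analysis plan. None is shown here, and the article is a condensed document, so the lack of an alpha split or testing order is not a fault in itself. That is right. It does not remove the conflict over what is primary, which lies in the published text and would remain whatever the analysis plan said.

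A reader might infer that the trial can claim success on whichever outcome, contrast or instrument works, with a false-positive rate several times 5%. The documents do not support that:

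- The sample size rests on an omnibus three-group ANOVA, and arm differences in consumption are tested by ANOVA. Six free pairwise tests are not described anywhere.
- The hypotheses are directional. Counting only errors in the hypothesised direction roughly halves the ungated figures. If Q1a and Q1c are read as requiring TOA to beat both comparators, the ungated chance falls further, to about 6% (ρ = 0) or 5% (ρ = 0.7). That reading is itself an assumption.
- Response is partly a threshold on Timeline-Follow-Back consumption, so correlations near zero, and the top of each range, are unlikely.
- The Hypotheses section predicts significant differences for consumption and the secondary outcomes. For response it predicts only a larger percentage of responders.
- The arm comparisons are placed at three months, and the analysis from three to six months is a separate SOA–TOA question. Consumption is measured with more than one instrument, but naming the scale for the mean comparison is ordinary analysis-plan detail.

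The outcomes section is also open about the composite nature of response, and the article argues for its clinical interpretability. That is a reason to report it prominently. It does not say how it combines with consumption.

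**Conclusion.** The point stands as an inconsistency in the definition of the primary outcome, with a moderate effect on error. With one three-arm test per primary at .05, the chance of a false primary claim is about 7 to 10% (ρ from 0.9 to 0), up to about twice the nominal level. It reaches about 17 to 23% only if all six contrasts are tested two-sided without a gate, or about 9 to 13% counting only the hypothesised directions. Several times 5% is therefore not the right summary.

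These figures assume no true arm differences, a range of ρ that the documents do not give, and .05 for the response test and for each contrast, which is inferred because the article states no other level. The ambiguity after a split result depends on none of these assumptions. The trial is not invalid, but the sections should be reconciled before results are seen.

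**What to change.** In the section on primary and secondary outcome measures, name weekly consumption by Timeline-Follow-Back at three months as the sole primary outcome, and make treatment response a key secondary outcome. This follows the outcome on which the trial is already sized and uses the instrument already chosen for response. The Aims should be aligned on timing, since they also list six months. Three months is where the Hypotheses place the arm comparisons, and the waiting-list arm is offered TOA after that point.

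State that the three-arm test is done at .05 and that the three pairwise contrasts follow at .05 only if it is significant. Present six-month, EuropASI and response results as supportive.

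The significance level and the Table 3 sample size do not change. The cost is that response can no longer carry the primary claim alone, and that a stated primary outcome is reclassified in an approved and registered trial, which should be documented.

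If the sponsor prefers to keep both as primary, it must state either that both have to succeed or how α is split. At .025 each, power of the consumption ANOVA at N = 150 is about 0.69, and N = 189 would be needed for .80.

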### Definition of treatment-response

Adding treatment-response criteria has an important advantage over the comparison of group mean-scores on primary and secondary outcome measures only. In our opinion, it has more external validity as it is helpful in making a clear statement on who actually improved to a clinical relevant extent. Based on binary treatment-response outcome data, we can calculate relative risk reduction, number needed to treat, and odds ratios. The British Medical Association published guidelines on sensible drinking which suggested that the boundaries for sensible alcohol consumption should be set at a maximum of 21 standard alcohol units per week for men, and 14 standard alcohol units per week for women [33]. To calculate treatment-response outcome, alcohol consumption as measured using Timeline-Follow-Back will be used [16]. Deteriation percentages relate to changes within participants on the secondary outcome measurement scores between t0 and t1. Treatment-response is defined as: *'alcohol consumption within British Medical Association boundaries, and less than 10% deteriation on any of the secondary outcome measures'*.

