### Study population

Our study population will be recruited through the SATCs website, that was viewed by 650.000 unique visitors in 2007 [14]. If necessary, additional attention for this study will be attracted through advertisements at family doctors' offices, internet-forums, and news-paper adds. Applicants meeting inclusion criteria defined in Table 1 are invited to participate.

**Table 1 T1:** Selection criteria for inclusion

**Inclusion criteria**	**Exclusion criteria**
age 18 – 64	prior therapy in addiction treatment centre
internet at home	history of alcohol delirium
AUDIT score > 8	history of drug overdose
alcohol consumption > 14 standard units per week	severe coronary problems
informed consent received	severe intestine diseases
	diagnosed schizophrenic
	history of stroke
	epilepsy in last year
	contemplated or attempted suicide in last year
	cocaine and or amphetamine use > 4 days last month
	cannabis use > 9 days last month
	holiday/travelling intention > 2 weeks during trial

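### Men drinking about 15–21 units a week at t0 can count as treatment responders in any arm without reducing their drinking

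*Protocol article*

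**What the plan says.** All places are in the Methods of the protocol article.

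- **Study population, Table 1.** Entry requires "AUDIT score > 8" and "alcohol consumption > 14 standard units per week". Neither criterion differs by sex, and no exclusion criterion removes men at the lower end of the consumption range.
- **Definition of treatment-response.** The limits are a "maximum of 21 standard alcohol units per week for men, and 14 standard alcohol units per week for women". Response is "alcohol consumption within British Medical Association boundaries, and less than 10% deteriation on any of the secondary outcome measures". For the consumption part, "alcohol consumption as measured using Timeline-Follow-Back will be used". The reason given for having the endpoint is "making a clear statement on who actually improved to a clinical relevant extent". Relative risk reduction, NNT and odds ratios are to be derived from it.
- **Primary and secondary outcome measures.** Treatment response is listed as a primary outcome alongside consumption. The secondary measures are AUDIT, QOL, EQ-5D, BSI, SF-HLQ and WAI-work.
- **Research questions.** Q1c, Q1f and Q3b are asked in terms of responders.
- **Measurement instruments, Table 2.** Timeline-Follow-Back is collected at t0, t1 and t2. Under Randomization, allocation follows completion of the t0 measurement.

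**The concern.** The endpoint is meant to separate people who improved from people who did not. Its consumption part describes only where a participant ends up, and for men that end state lies partly inside the range in which they may enter. The second part asks only that things have not become worse. Someone who stays exactly as he was can satisfy both.

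At stake are the meaning of a primary outcome and the measures built on it. Participants who qualify without change raise the response rate in every arm, the waiting list included. That pulls the risk ratio and odds ratio toward 1, raises the NNT and costs power. Because the overlap is mainly in men, the absolute response rates would also depend on the sex mix of the sample.

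**Working it through.** **Overlap of the two rules**

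| | Entry | Within response limit | Both |
|---|---|---|---|
| Men | > 14 | ≤ 21 | > 14 to 21 (whole units 15–21) |
| Women | > 14 | ≤ 14 | none |

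A man at, say, 18 units at t0 and at follow-up is within the limit. If his secondary scores are unchanged, deterioration is 0%, below the 10% threshold. He meets the whole definition in any arm.

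**Size: inputs**

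The article gives no expected response rates and no share of participants already within limits, so there is no figure of its own to reproduce for this endpoint. The sample size in Table 3 concerns consumption and does not bear on it. The following are assumptions:

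- true response among participants above their limit at t0: p₀ = 0.10 on the waiting list, p₁ = 0.30 in Therapy Online Alcohol (TOA);
- share already within limits at t0: s = 0.05, 0.10 or 0.20;
- worst case: every such participant responds in every arm.

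**Formulas**

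Observed rate = s + (1 − s)p. RR = rate₁/rate₀. OR is the ratio of the odds. NNT = 1/(rate₁ − rate₀).

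| s | Waiting list | TOA | RR | OR | NNT |
|---|---|---|---|---|---|
| 0 | 0.100 | 0.300 | 3.00 | 3.86 | 5.00 |
| 0.05 | 0.05 + 0.95 × 0.10 = 0.145 | 0.05 + 0.95 × 0.30 = 0.335 | 2.31 | 2.97 | 5.26 |
| 0.10 | 0.10 + 0.90 × 0.10 = 0.190 | 0.10 + 0.90 × 0.30 = 0.370 | 1.95 | 2.50 | 5.56 |
| 0.20 | 0.20 + 0.80 × 0.10 = 0.280 | 0.20 + 0.80 × 0.30 = 0.440 | 1.57 | 2.02 | 6.25 |

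**Relaxing the worst case at s = 0.10**

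- Such participants respond at 50% in both arms: 0.05 + 0.09 = 0.14 and 0.05 + 0.27 = 0.32. RR is 2.29 and NNT 5.56.
- They respond at 50% and 70%: 0.05 + 0.09 = 0.14 and 0.07 + 0.27 = 0.34. RR is 2.43, OR 3.16 and NNT 5.0.

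The ratios depend on how many of these participants respond. The NNT depends only on whether treatment changes their response.

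**Power**

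A second assumed pair, 15% and 40%, is used with 50 per arm (section Randomization). The test is two-sided at 5%, normal approximation with pooled variance under the null. With p̄ the mean of the two rates, power = Φ{[|rate₁ − rate₀| − 1.96√(2p̄(1 − p̄)/n)] / √([rate₀(1 − rate₀) + rate₁(1 − rate₁)]/n)}. The right-hand column analyses only participants above their limit at t0, n = 50(1 − s) per arm, at the undiluted rates.

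| s | Rates under the article's definition | Power, n = 50 | Power, restricted set |
|---|---|---|---|
| 0 | 0.150, 0.400 | 81% | 81% |
| 0.10 | 0.235, 0.460 | 66% | 77% (n = 45) |
| 0.20 | 0.320, 0.520 | 53% | 71% (n = 40) |

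Under the same worst-case assumption, the smaller denominator costs less power than the dilution does.

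**The case against.** The overlap itself cannot be argued away, but four objections limit what follows from it.

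**Screening is not t0.** Under Procedures, eligibility is checked by a web questionnaire; no instrument is named for the consumption criterion and the size of a unit is not defined. Response uses Timeline-Follow-Back, and t0 comes later, after a consent period with no time limit. A reader might infer that no woman can be within her limit at baseline. That holds only for the screening criterion: a woman screened just above 14 may be at or below it on t0 Timeline-Follow-Back, and a man screened at 18 may be above 21. This objection stands. It blurs the edges of the band without removing it.

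**Not every such man will respond.** Consumption fluctuates, and six secondary measures must each avoid a 10% deterioration. A reader might infer that all of these men are automatic responders; the article does not support that. This stands too, and makes the calculated dilution an upper bound.

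**The comparison between arms remains valid.** Being within limits at t0 is a pre-randomisation feature, expected equally in all arms. A reader might fear a spurious treatment effect, but nothing in the design produces one. This stands. The sample size also rests on consumption, and the Abstract and Aims name only consumption as primary; response is added in the outcome section. These points lower the severity.

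**An end-state definition is legitimate.** Being within sensible limits and no worse can be a reasonable goal. The article, however, justifies the endpoint by improvement, which the definition does not require. Adjusting the logistic regression for t0 consumption would not change who is counted as a responder, nor the crude NNT and relative risk reduction.

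**Conclusion.** The point holds as a should-fix. The entry floor and the male response limit overlap at about 15–21 units a week, and no reduction from t0 is required. A primary outcome introduced to show improvement can therefore be met without any, provided no secondary measure deteriorates by 10% or more.

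The consequence is dilution toward the null and inflated response rates. How much is unknown: the share of participants within limits at t0 is not given, and the AUDIT criterion may make the group small although it does not exclude it. The RR range of 2.3–1.6 and the NNT range of 5.3–6.3 rest on assumed true rates of 10% and 30%, assumed shares of 5–20%, and response by every such participant in every arm. They are worst cases, not estimates. At the smaller shares the NNT hardly moves; the ratios and the waiting-list rate (10% rising to 14.5–28% across the range) are affected more. The stronger conclusion, that the response analysis is invalid or would favour treatment falsely, is not supported.

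**What to change.** 1. Define response as moving from above the sex-specific limit on Timeline-Follow-Back at t0 to within it at follow-up, keeping the existing non-deterioration condition. The limits themselves are unchanged.
2. Analyse it in all randomised participants who were above their own limit at t0. The set is fixed by a measurement taken before allocation, so the comparison between arms stays randomised. It also deals with any woman within her limit at t0.
3. Keep all randomised participants in the consumption analysis.
4. Report the end-state definition in all randomised participants as a sensitivity analysis, showing those within limits at t0 separately.

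This takes a few sentences in the response definition and the analysis section, and no new data. The cost is a smaller denominator for the response analysis, by the share within limits at t0: 5%, 10% or 20% of 150 would be about 8, 15 or 30 participants, so the loss could be more than slight. The primary response analysis would no longer cover everyone randomised, which is why the sensitivity analysis is needed. The change also does not set a minimum improvement: a man going from 22 to 21 units would still count. The wording about clinically relevant improvement should be matched to what the revised definition delivers.
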